### Secondary outcomes

#### Self-reported physical activity

Self-reported physical activity will be assessed with a newly developed questionnaire (Simple Physical Activity Questionnaire (SIMPAQ)) specifically developed for the use with psychiatric patients [118]. Validation of this instrument with psychiatric patients is currently underway (see www.simpaq.org). Data for healthy people show that the instrument is reasonably associated with objectively assessed physical activity [119]. The SIMPAQ uses an interview format (5–10 min in duration) to assess time in bed, structured exercise participation, and incidental or non-structured physical activity. Data from our research group assessed in university students show that moderate-to-vigorous physical activity estimated with the SIMPAQ correlates moderately to highly with accelerometer data (*r* = 0.30–0.70) [119]. The same public health recommendations apply as for objectively measured physical activity [91].

#### Cardiorespiratory fitness

The Åstrand and Rodahl indirect test of maximal oxygen uptake (VO_2_max) will be used to assess cardiorespiratory fitness [120]. The test will be performed on a bicycle ergometer (Bike Forma; Technogym) at the same time of the day (starting between 08:00 and 10:00). This test has been validated for the purposes of measuring submaximal fitness [120]. The pedalling frequency during the Åstrand test will be set at 50 rpm, and the workload adjusted so that the heart rate is kept between 130 and 160 beats per minute (bpm) in participants younger than 40 years old and between 120 and 150 bpm in participants older than 40 years old. To ensure that participants maintain their exercise intensity level at 13 or 14 (slightly strenuous), we will employ the Borg Rating of Perceived Exertion scale [121]. When the heart rate remains stable after 5 or 6 min, a steady state is reached. Peak oxygen uptake (l/min) will be estimated based on mean steady state, sex, and power output, using a nomogram [120], and including a correction factor for age. After correction of body weight, oxygen uptake will be expressed as peak VO_2_max (ml/kg/min). Gender and age-adjusted cut-off values will be used to categorize participants into groups with low, moderate, and high CRF [66]. The reliability and validity of the Åstrand nomogram and linear extrapolation for deriving VO_2_max has been documented in a previous study [122].

#### Autonomic function

Using heart rate monitors (V800; Polar Electro, Finland), following a 5-min period of rest, R–R intervals will be recorded over 5 min; based on their variation, the heart rate variability (HRV) is calculated. This non-invasive method allows for the accurate evaluation of autonomic nervous system activity [123]. Recorded R–R intervals will be processed and analysed with Kubios HRV [124]. Evidence for the validity of the Polar V800 monitor for the assessment of HRV at rest has been documented in a prior study [125]. In the time domain, the standard deviation of normal-to-normal intervals (SDNN) and the root mean square of standard deviation (RMSSD) will be examined. Additionally, low-frequency power (LF nu; bandwidth 0.04–0.15 Hz) and high-frequency power (HF nu; bandwidth 0.15–0.4 Hz), expressed as normalized units, as well as the LF nu/HF nu ratio will be examined as frequency-based HRV parameters. To the best of our knowledge, no MCID scores are currently available for HRV [126].

#### Perceived fitness

A one-item proxy measure is used to assess subjectively perceived physical fitness [127]. The following item will be used: “Overall, how would you rate your physical fitness?” Answering options range from 1 (very poor fitness) to 10 (excellent fitness). The validity of this item as an indicator of perceived fitness has been established previously. High correlations were found with the 12-item Perceived Physical Fitness scale [128]. Moreover, this measure proved to be reasonably associated with objective physical fitness, perceived well-being, and sleep [128, 129]. No MCID scores exist for this measure.

#### Exercise-related self-efficacy

Three items referring to beginning, maintaining, and restarting exercise after a relapse are used to assess exercise-related self-efficacy beliefs (e.g. “I feel confident to start with a new exercise activity”) [130]. This scale proved to be a psychometrically sound measure in a previous study [130] and has been used in previous intervention studies [80–82, 131]. The scale ranges from 0 (not at all confident) to 5 (100% confident in myself). The three items are added to obtain a single score. No MCID scores exist for this measure.

#### Exercise-related outcome expectancies

Nine positive (‘pros’; e.g. “I can improve my physical appearance if I regularly exercise”) and seven negative formulated items (‘cons’; e.g. “If I exercise, I end up in situations where I feel embarrassed”) are used to assess outcome expectancies [132]. The items are anchored on a 4-point Likert-type scale from 1 (not true) to 4 (completely true). Satisfactory psychometric properties of these items have been demonstrated [132]. Items are combined into two composite scores (positive and negative) by the arithmetic mean of each. No MCID scores exist for this measure.

#### Exercise intention

One item is used to assess exercise-related goal intentions [130]. More specifically, participants are asked about the strength of their intention to exercise regularly during the next few weeks and months (0 = no intention to 5 = very strong intention). This measure proved to have acceptable reliability and validity in previous studies [133, 134]. No MCID scores exist for this measure.

#### Exercise-related self-concordance

Exercise-related self-concordance is assessed with the 12-item SSK scale [133], which is consistent with the self-concordance model by Sheldon and Elliot [135]. The SSK scale consists of four subscales that assess the intrinsic (e.g. “I (would) exercise because it’s just fun for me”), identified (e.g. “I (would) exercise because I have good reasons to be physically active”), introjected (e.g. “I (would) exercise because otherwise I would have a guilty conscience”) and extrinsic (e.g. “I (would) exercise because others tell me to become physically active”) reasons for exercising. All items are answered on a 6-point Likert scale from 1 (not at all true) to 6 (completely true). An overall index is built by summing the identified and intrinsic mean scores and subtracting the introjected and extrinsic mean scores. The reliability and validity of this instrument have been established previously [133]. No MCID scores exist for this measure.

#### Action planning

Five items with established reliability and validity are administered to collect information about participants’ level of action planning [134, 136]. These items assess the degree to which individuals have pre-planned their exercise participation. Thus, participants are asked whether they normally make plans when, where, how, how often, and with whom they exercise. Answers range from 1 (not at all true) to 4 (completely true). The item scores are summed to obtain an overall index. No MCID scores exist for this measure.

#### Perceived exercise barriers

A 19-item scale that lists various obstacles to regular exercise participation is used to measure perceived exercise barriers [137]. Satisfactory psychometric properties of this instrument were reported previously [68, 137, 138]. Participants indicate on a 4-point Likert scale from 1 (almost never) to 4 (almost always) how often they perceive these barriers (e.g. “I have too much work to do”). The mean is computed to obtain a single score. No MCID scores exist for this measure.

#### Coping planning

A 5-item index is used to gain insight into coping planning [136]. Participants are asked to what degree they use self-regulation strategies to overcome potential exercise barriers (e.g. “I have made a detailed plan regarding what to do in difficult situations in order to act in according to my intentions”). Answers range from 1 (not at all true) to 4 (completely true). The item scores are summed up to obtain a composite index. The reliability and validity of this scale have been established previously [134, 136]. No MCID scores exist for this measure.

#### Exercise-related social support

A seven-item index is used to assess social support from relevant others (e.g. “Close family or friends help me plan my exercise”) [132]. Answers are given on a 4-point Likert scale with values from 1 (almost never) to 4 (almost always). This scale proved to be a psychometrically sound measure in previous studies [131, 132]. No MCID scores exist for this measure.

#### Depression severity

The HAMD17 total score [95] and the Beck Depression Inventory (BDI) [97, 98] are used to assess depression severity. The BDI is a 21-item tool frequently used to assess symptoms of unipolar depression such as affective, behavioural, cognitive, and somatic symptoms (e.g. “I am so unhappy/sad that I can’t stand it”). Four response options exist, which reflect increasing levels of depressive symptomatology. The HAMD17 and BDI total scores range from 0 to 52 and from 0 to 63, respectively, with higher scores reflecting stronger depressive symptoms. The reliability and validity of the HAMD17 [139, 140] and the BDI [141] are well documented in the scientific literature. Response and remission are defined based on the HAMD17 scores. Response is defined as ≥ 50% decrease of symptoms from baseline to the endpoint, partial response as 25–49% reduction, and non-response as < 25% reduction, whereas remission is accomplished if the HAMD17 total score is ≤ 7 [142]. With regard to the BDI, scores between 0 and 9 indicate that a person is not depressed, scores between 10 and 18 reflect mild–moderate depression, scores between 19 and 29 indicate moderate-to-severe depression, and scores ≥ 30 indicate severe depression [97]. Button et al. [143] further suggested for the BDI that the MCID is best measured on a ratio scale, with a reduction of 17.5% of the initial scale representing a clinically meaningful change in depressive symptoms.

#### Self-perceived stress

Perceived stress will be assessed with the Perceived Stress Scale (PSS) [144, 145]. The 10-item PSS is a well-established self-report measure of stress and is based on the cognitive-transactional stress theory. Answers are given on a 5-point Likert scale ranging from 1 (never) to 5 (very often). Evidence for the validity and reliability of the PSS has been reported previously [146]. No MCID scores exist for this measure.

#### Self-perceived health

The Medical Outcomes Study 12-Item Short Form Health Survey (SF-12) is used to assess participants’ self-perceived health [147]. This instrument is among the most widely used measures within general population research [148], and the reliability and validity of the SF-12 are well documented [149, 150]. The composite scores of both subscales (physical and psychological health) are calculated by weighting each item as described in the SF-12 manual. Higher scores reflect increased health functioning. A study with low back pain patients suggests that improvements of > 3.77 in the psychological subscale and of > 3.29 in the physical subscale can be regarded as suitable MCID scores [151].

#### Insomnia symptoms

Sleep complaints are assessed with the seven-item Insomnia Severity Index (ISI) [152]. Answers are given on a 5-point rating scale, ranging from 0 (not at all) to 4 (very much). Evidence for the reliability and validity of this instrument has been documented previously [153, 154]. These items are in line with DSM-IV criteria for insomnia and include symptoms such as difficulties falling asleep, difficulties maintaining sleep, early morning awakening, increased daytime sleepiness, low daytime performance, low satisfaction with sleep, and worrying about sleep. Higher scores reflect a higher level of sleep complaints. Scores of 0–7 indicate absence of insomnia, scores of 8–14 indicate subthreshold insomnia, scores of 15–21 indicate moderate insomnia, and scores of 22–28 indicate severe insomnia [153].

#### Cognitive function

Today, there is no gold standard regarding the assessment of cognitive and executive function [155]. With regard to cognitive function, we decided to apply an odd-ball paradigm, the two-back test, and the Flanker task to assess sustained attention, working memory, and inhibition, respectively. The odd-ball paradigm [156] requires participants to press a button to deviants, which appear with a lower frequency (25%) than standard stimuli (75%). In the two-back task [157], participants are instructed to identify whether or not the presented letter matches the one presented two trials before by pressing a button corresponding to yes or no. Lastly, the Flanker task [158] requires participants to respond to the direction of a centrally presented arrow and to ignore the flanking arrows, which either point in the same or the opposite direction. These computer-based cognitive tests are well recognized neuropsychological tests for assessing attention [159] and executive function [160], and have been found to be reliable tools in previous research [161–163]. In the present study, the cognitive tasks will be administered with E-Prime 3.0 (PST, USA). Separately for each test, the reaction time (on response-correct trials) and accuracy will be extracted for statistical analyses. No established MCID scores exist for this measure.

#### Blood pressure

Systolic (SBP) and diastolic (DBP) blood pressure will be measured after the participant has rested for 5 min while seated. Blood pressure is taken twice within 5 min with the Omron® digital blood pressure monitor. A cuff size appropriate to the arm circumference of the participants will be chosen. Evidence for the validity of Omron® oscillometric blood pressure measurement devices has been reported previously [164]. Reductions in SBP and DBP of 2 mmHg are considered meaningful MCID scores [165]. Participants will be considered hypertensive if they have SBP scores of ≥ 140 mmHg and DBP scores of ≥ 90 mmHg [166].

#### Body mass index, percentage of body fat, and waist circumference

Body weight will be measured with a digital weighing scale (BC-545; Tanita, USA) without shoes (to the nearest 0.1 kg, in light clothes). To measure height, each participant will stand against a stadiometer without shoes. Body height will be taken (to the nearest 0.5 cm). BMI will be calculated with the following formula: weight (kg) / (standing height (m))^2^. Based on WHO standards [167], participants will be classified as overweight if their BMI is ≥ 25.0 kg/m^2^, and as obese with a BMI of ≥ 30.0 kg/m^2^. Following an expert consensus [168], 5% weight loss is considered the MCID among people classified as overweight or obese. The BC-545 weighing scale can also be used for bioelectrical impedance analysis to assess percentage body fat. With regard to healthy body fat, the WHO [167] recommends maximum levels of ≥ 32% for women and ≥ 25% for men. In the present study, a reduction of 2% is defined as the MCID for percentage body fat [169]. A flexible tape at the natural waist (halfway between the ribcage and the iliac crest) is used to determine waist circumference. The expert panel of the National Cholesterol Education Program [170] defines a waist circumference of ≥ 80 cm (women) and ≥ 94 cm (men) as a risk factor for metabolic syndrome.

#### Cholesterol, triglycerides, and HbA1c

To perform blood tests, venous blood is drawn between 07:00 and 08:30 after fasting since 22:00 the day before by a trained nurse. For the assessment of blood lipid profiles (total cholesterol (TC), low-density-lipoprotein cholesterol (LDL-C), high-density-lipoprotein cholesterol (HDL-C), and triglycerides (TG)) and HbA1c, blood samples will be analysed via the Afinion test (Alere Technologies; Abbott, Wädenswil, Switzerland). One drop of blood will be taken up by the test strip and read by the machine. Good correspondence exists between the Alere point-of-care (PAC) analyser results and reference laboratory tests for HbA1c and lipid levels [171, 172]. Following Rodondi et al. [173], the following clinically relevant cut-off values should be considered for total cholesterol (≥ 5.6 mmol/l), HDL-C (≤ 1.41 mmol/l), and LDL-C (≥ 3.40 mmol/l). To our knowledge, no officially established MCID score exists for cholesterol levels, although some authors suggested considering a 10% increase in HDL-C and a 10% decrease in LDL-C as a meaningful score [174]. Following the American Diabetes Association [175] and the WHO [176], HbA1c scores of 5.7–6.4% point towards pre-diabetes, whereas scores of ≥ 6.5% can be used as diagnostic cut-off point for diabetes, and reductions of ≥ 0.5% are generally considered the MCID for type 2 diabetes [177].

#### Brain-derived neurotrophic factor

Serum BDNF levels [178] will be determined in duplicate with an enzyme-linked immunosorbent assay (BDNF Emax Immunoassay System; Promega, USA). This method showed intra- and inter-assay variation coefficients of 6.0 and 8.5%, respectively [179]. No MCID scores exist for this measure.

#### Tumour necrosis factor alpha

The solid-phase Enzyme Amplified Sensitivity Immunoassay TNF-α ELISA from DRG (Switzerland) will be used to assess TNF-α [178]. The assay uses monoclonal antibodies (mAbs) directed against distinct epitopes of TNF-α. The amount of substrate turnover is determined colourimetrically by measuring the absorbance, which is proportional to the TNF-α concentration. No MCID scores exist for this measure.

#### Insulin-like growth factor 1

The DRG IGF-I 600 ELISA Kit (DRG), a solid phase enzyme-linked immunosorbent assay (ELISA), based on the principle of competitive binding, will be used to assess IGF-1 [180]. Patient samples, standards, and controls are acidified and neutralized prior to the assay procedure. No MCID scores exist for this measure.

### Moderator

#### Serotonin transporter gene (5-HTTLPR)

To assess the 5-HTTLPR genotype [181] at baseline, 9 ml EDTA blood is collected from each participant (patients and controls). Within 2 h the blood sample is centrifuged without a break at 2500 × *g* for 10 min at room temperature to separate the cellular components. White blood cells are enriched in the resulting intermediate layer, which is carefully transferred to a reaction tube and stored at − 20 °C for no longer than 4 weeks prior to further processing. The next steps involve DNA extraction according to the manufacturer’s instructions using the QUIAamp DNA blood mini kit (Quiagen, Switzerland), 5-HTTLPR-specific DNA amplification using GoTaq Polymerase and the Promega PCR Master Mix (Promega), and the following 5-HTTLPR primers: forward, GGC GTT GCC GCT CTG AAT GC (annealing temperature 66 °C); and reverse, GAG GGA CTG AGC TGG ACA ACC AC (annealing temperature 74 °C). After completion of the PCR, the products are electrophoretically evaluated.

The four afore-mentioned biochemical and genetic analyses for BDNF, TNF-α, IGF-1, and 5-HTTLPR will be performed at the Neurobiological Laboratory of the Psychiatric University Clinics Basel ([name]).

### Covariates

The following variables will be assessed as potential covariates. Based on participants’ self-reports, we will assess their gender, age, language, nationality, marital status, level of education, employment (rate) prior to hospitalization, years of job experience, smoking status, and the number of children living at home. In addition, based on a clinical interview with the treating psychiatrist, we will assess information regarding duration of the current depressive episode, number of prior depressive episodes, age of onset of depression, and current medication.

### Qualitative data assessment

A nested qualitative study will be carried out using semi-structured interviews to assess the experience and acceptability of the intervention for the patients. All interviews will be tape-recorded, transcribed, and analysed with qualitative content analysis [182]. Moreover, the physical activity facilitator will register the number of hours needed for the counselling of each patient. As a result, we will be able to calculate the costs that need to be covered by a clinic if a trained professional is employed to facilitate physical activity adoption and maintenance. To assess cost-effectiveness of a physical activity intervention, Baxter et al. [87] and Chalder et al. [88] used a similar procedure in a previous study.

### Data collection and statistical analysis

Types of data to be collected include: quantitative data on social and demographic background, anthropometric measurements, physical activity, cardiorespiratory fitness, exercise-related variables (cognitive and social determinants), indicators of psychological functioning, cardiovascular risk factors, and biomarkers of MDD; and qualitative data, based on semi-structured interviews, on the acceptability and perceived usefulness of the intervention among the patients. The collected data will be entered and merged into a single datafile. Statistical analysis will be performed using SPSS.

Treatment group, age, gender, baseline HAMD17 score, and the amount of previous depressive episodes will be selected as covariables. Changes in outcome variables over the three time points will be analysed using repeated-measures analyses of covariance (rANCOVAs), with a between-subject factor group (IG vs PCG) and a within-subject factor time (baseline, post intervention, follow-up). If significant group or time interactions are present, Bonferroni-adjusted post-hoc tests will be performed to identify individual differences. The statistical significance level will be defined at α = 0.05. Effect sizes will be calculated according to the recommendations of Cohen [183], with 0.49 ≥ *d* ≥ 0.20 indicating small effect (e.g. negligible practical importance), 0.79 ≥ *d* ≥ 0.50 indicating medium effect (moderate practical importance), and *d* ≥ 0.80 indicating large effect (crucial practical importance).

In the case of missing values (e.g. when patients drop out before follow-up), all analyses will be performed with and without intention to treat [184]. After a thorough dropout analysis, a decision will be reached regarding the method best suited to analyse intention-to-treat effects (e.g. last observation carried forward, imputation of missing values) [185].

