**Methods:**

The study is designed as a multi-centric two-arm randomized clinical trial including an intervention group and a placebo control group, allocation concealment, single-blinding, and intention-to-treat analysis. Participants (*N* = 334) will be continuously recruited from four clinics specialized in the treatment of MDD. The intervention builds on a standardized, theory-based, low-cost lifestyle physical activity counselling programme, which was specifically designed for an in-patient rehabilitation setting. The placebo control condition consists of general instructions about health-enhancing physical activity. Data assessments will take place 2–3 weeks after admission to in-patient treatment (baseline), and 6 weeks (post) and 12 months (follow-up) after discharge from in-patient treatment. The primary outcome is objectively assessed physical activity at follow-up.

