### Participants

#### Recruitment and power calculations

Clinical in-patients aged 18–65 years with a current diagnosis of major depression (ICD-10) will be continuously recruited from the Psychiatric Services Solothurn, Psychiatric Clinics of the University of Basel, Psychiatric Clinic Wyss, Münchenbuchsee, and the Psychiatric Clinic Sonnenhalde, Riehen. In previous studies with non-depressed individuals, individually tailored physical activity promotion was associated with a moderate effect (*d* = 0.50) on the primary outcome (physical activity) [80, 81]. So far, only one study exists examining physical activity counselling among out-patients with depression, yielding an adjusted odds ratios of 2.27 across the 4-month, 8-month, and 12-month follow-up (corresponding *d* = 0.45). Conversely, a relatively small effect size (*d* = 0.28) was observed in a Cochrane review of intervention studies promoting physical activity among generally healthy people [92]. Similarly, remote interventions such as telephone-based, app-based, and Internet-based coaching versus a control group were associated with rather small effect sizes for change in physical activity (*d* = 0.20) [93]. Given these observations, we assume a small-to-moderate effect of our intervention on the primary outcome (*d* = 0.30). Accordingly, the optimal sample size to detect a significant effect at follow-up is 278 participants (two independent groups, one-tailed, α-error probability = 0.05, power = 0.80). With 20% expected dropouts from baseline to follow-up [94], the targeted sample size is *N* = 334 (IG, *n* = 167: PCG, *n* = 167). This means that every centre will recruit approximately 40 participants per year (*n* = 20 in the IG, *n* = 20 in the PCG). Dependent on the size of the clinics, this corresponds to a recruitment rate of 20–25% of the patients. Enrolment will be systematically monitored by the sponsor-investigator in order to recruit a sufficient number of participants within the planned timeframe.

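### The primary outcome and sample size concern one 12-month group comparison, but the only stated analysis is a three-time-point interaction that gates Bonferroni post-hoc tests

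*Protocol article*

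**What the plan says.** The abstract (Methods) fixes both endpoint and time point: "The primary outcome is objectively assessed physical activity at follow-up".

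The section on recruitment and power calculations sizes the trial for that comparison: "the optimal sample size to detect a significant effect at follow-up is 278 participants", from d = 0.30 and "two independent groups, one-tailed, α-error probability = 0.05, power = 0.80". After dropout the target is 334, or 167 per arm.

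The section on data collection and statistical analysis describes something else for all outcomes. It is a repeated-measures ANCOVA with group as the between-subject factor and time as a within-subject factor whose three levels include baseline. The covariate sentence reads: "Treatment group, age, gender, baseline HAMD17 score, and the amount of previous depressive episodes will be selected as covariables". Baseline activity is not among them. The follow-on rule is: "If significant group or time interactions are present, Bonferroni-adjusted post-hoc tests will be performed to identify individual differences". The number of comparisons in the Bonferroni family is not given. Alpha is 0.05, and this section does not state sidedness.

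**The concern.** The endpoint and the sample size call for a single between-group contrast at 12 months. The analysis section instead leads with a two-degree-of-freedom group-by-time test, and as written the 12-month comparison is reached only through it. Two things are at stake.

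First, the leading test can be significant for a reason unrelated to the primary outcome, namely an early effect that fades. The article's own background section reports that, in a similar counselling programme for orthopaedic in-patients, the group difference shrank by 12 months, so this scenario is realistic.

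Second, the 80% power was computed for a test that the analysis section does not specify. The choice between the two routes could decide whether the trial is called positive.

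**Working it through.** **Inputs from the article.** d = 0.30 at follow-up (SD = 1); one-tailed alpha 0.05; power 0.80; 278 evaluable, so 139 per arm; three time levels including baseline.

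**Assumptions (the article gives none of these).** Common correlation ρ between visits of 0.3, 0.5 or 0.7; 6-week effect d₁ of 0.3 or 0.5; Bonferroni over three comparisons, or no reduction of alpha.

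**Step 1: the plan's own figure.** Normal approximation: n per arm = 2(1.645 + 0.842)²/0.30² = 137.4, so 138. The t-test solution is 138.07, rounded up to 139, and 2 × 139 = 278. Power at 139 per arm is 0.802 one-tailed. The figure reproduces, but only for a single-time-point two-group test. The same test two-sided has power 0.703.

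**Step 2: what the interaction responds to.** Noncentrality λ = (n/2) Σ(δₜ − δ̄)²/(1 − ρ), with 2 and 2(2n − 2) = 552 df.

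- Effect 0.3 at 6 weeks, zero at 12 months: Σ = 0.01 + 0.04 + 0.01 = 0.06, so λ = 69.5 × 0.06/(1 − ρ) = 5.96, 8.34, 13.9. Power is 0.58, 0.73, 0.92 for ρ = 0.3, 0.5, 0.7.
- Effect 0.5 at 6 weeks, zero at 12 months: Σ = 0.1667, λ = 16.5, 23.2, 38.6. Power is 0.96, 0.99, 1.00.

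So the interaction is significant in 58% to 100% of such trials. The 58% needs every correlation to be 0.3. If the two post-baseline visits correlate with each other at 0.5 or more, the range is about 70% to 100%.

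Σ is also 0.06 for effects (0, 0, 0.3) and (0, 0.3, 0.3) at baseline, 6 weeks and 12 months. The test has identical power for an effect at 6 weeks only, at 12 months only, or at both.

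**Step 3: detecting d = 0.30 at 12 months, 139 per arm.** The gated columns come from simulation (8,000 trials per row): interaction significant at 0.05 and follow-up t-test, not adjusted for baseline activity, significant in the right direction. The ANCOVA column uses d/√(1 − ρ²) = 0.3145, 0.3464, 0.4201, two-sided at 0.05.

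| d₁ | ρ | Interaction alone | Gate + follow-up at 0.05/3 | Gate + follow-up at 0.05 | ANCOVA on baseline |
|---|---|---|---|---|---|
| 0.3 | 0.3 | 0.58 | 0.36 | 0.44 | 0.74 |
| 0.3 | 0.5 | 0.73 | 0.43 | 0.54 | 0.82 |
| 0.3 | 0.7 | 0.92 | 0.51 | 0.66 | 0.94 |
| 0.5 | 0.3 | 0.90 | 0.48 | 0.63 | 0.74 |
| 0.5 | 0.5 | 0.97 | 0.53 | 0.69 | 0.82 |
| 0.5 | 0.7 | 1.00 | 0.53 | 0.70 | 0.94 |

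Letting the post-baseline visits correlate differently from baseline, and allowing for simulation error, widens the gated ranges only slightly, to about 0.35–0.54 and 0.42–0.71. A 6-week effect of 0.15 lowers the bottom of each range to 0.33 and 0.39 (ρ = 0.3). With 334 × 0.8 / 2 ≈ 134 completers per arm, the ANCOVA gives 0.73, 0.81, 0.93.

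**The case against.** **Halved power.** A reader might infer that the plan roughly halves power. The documents do not support that as a general statement. They give no Bonferroni family size, correlation or 6-week effect. With two groups, a between-group comparison at one time point is a single test, and on that reading Bonferroni changes nothing. Gated power as a share of ANCOVA power runs from 0.36/0.74 = 0.49 to 0.53/0.82 = 0.65 with the divisor of three, and from 0.44/0.74 = 0.59 to 0.63/0.74 = 0.85 without it. A half appears only when the gate, the divisor and an unadjusted post-hoc test are stacked and the correlation or 6-week effect is unfavourable.

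**The gate is one reading.** The phrase about group or time interactions is ambiguous, and the interaction itself might be meant as the group test. Its power alone reaches 0.92 to 1.00 at ρ = 0.7, close to or above the ANCOVA. That stands, but such a result would still not be specific to 12 months. If the post-hoc step were a change-score contrast, power would be 0.56, 0.70 and 0.90 against 0.74, 0.82 and 0.94, a smaller loss.

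**Sidedness.** The fall from 0.80 to 0.70 on moving from one-tailed to two-sided testing is a separate issue and should not be charged to the repeated-measures design. The ANCOVA comparison above is two-sided throughout.

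**Unseen documents.** A full protocol or analysis plan may name the 12-month contrast. That would not remove the mismatch: the article fixes a model, a gate and a multiplicity rule that do not fit its own endpoint and sample size.

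**Covariate list.** Naming treatment group as a covariable as well as the factor might look like a modelling error. It is a wording slip with no effect on the fitted model.

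**Conclusion.** The mismatch is real and follows from the text alone: the endpoint and sample size concern one 12-month comparison, while the stated analysis is a three-level interaction with gated, Bonferroni-adjusted post-hoc tests and baseline activity as an outcome level. The 80% power belongs to a different test.

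The size is conditional. If the interaction and an unadjusted follow-up test must both succeed, power for d = 0.30 is about 0.35–0.54 with three Bonferroni comparisons and about 0.42–0.71 with no reduction of alpha, against about 0.73–0.94 for a two-sided baseline-adjusted ANCOVA. These ranges rest on normal data, correlations of 0.3 to 0.7 and 6-week effects of 0.3 to 0.5.

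A reader might also infer bias or an inflated type I error for the 12-month test. Neither has been shown: the gated route is conservative for that test. The harm is lost power, and a lead test that can be significant without any 12-month effect.

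**What to change.** In the section on data collection and statistical analysis, name as the primary analysis a single arm contrast in 12-month objective activity. Use an ANCOVA, or a mixed model with post and follow-up activity as outcomes. Adjust for baseline activity, the stratification factors (age, gender, clinic), baseline HAMD17 and number of previous episodes; baseline activity and clinic are the additions to the present list. Test at alpha = 0.05, with sidedness stated and consistent with the sample-size section. Apply no interaction gate and no Bonferroni adjustment to this contrast. Make the group-by-time interaction and the 6-week contrast secondary, and give the size of any Bonferroni family that remains. Drop treatment group from the covariate list as a tidy-up.

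The cost is wording only. All the variables are already collected and the planned software can fit the model. The change should be recorded before outcome data are analysed by arm.
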